### Data governance and ethical considerations

We will respect the Tri-Council Policy Statement, Chapter 9, which highlights the importance of engaging with First Nations throughout all phases of the research process. In addition, we will honour Indigenous knowledge by engaging with Elders and the Mamaweswen Council. Anonymized data collected at Benbowopka will be linked in accordance with data governance protocols and the data-linkage process will be established at ICES in consultation with the Chiefs of Ontario. All parties involved in the study will respect Indigenous principles of OCAP [43].

### Ethics

This research will be conducted in keeping with the Canadian Institutes of Health Research (2011) *Guidelines for Research Involving Aboriginal People* and the *Tri-Council Policy Statement for Ethical Conduct for Research Involving Humans* [44]. The study received approval from Laurentian University’s Ethics Board in May 2017.

### Training

Wellness, training, and capacity building will be the cornerstones of this research. Clinicians at Benbowopka were trained in the IHSS methodology (beginning January 2016) and IHSS is now routinely delivered to patients.

The five days of training on the IHSS program incorporates all of the elements of an integrative Two-Eyed Seeing and blended approach [45]. The training consists of didactic, experiential, and small-group learning. During the training the clinicians engage in IHSS sharing circle sessions such as Post Traumatic Stress Disorder (PTSD), taking back your power, setting boundaries in relationships, dealing with anger, and taking good care of yourself [46]. The design and delivery of this training is consistent with previous experience training IHSS facilitators by this research team [36, 47]. During these sharing circles the Elder offers a Grandfather teaching, Indigenous spiritual and traditional sayings, smudging, and/or prayers. The teachings of the Seven Grandfathers, also known as either the Seven Teachings or Seven Grandfathers, are a set of teachings on human conduct toward others. They include the concepts of wisdom, love, honesty, respect, bravery, humility, and truth [48]. The day starts with didactical presentations until lunchtime, and in the afternoon the clinicians engage in an actual IHSS sharing circle facilitated by the first researcher and an Elder. The clinicians have opportunities to ask questions, and through this in-depth discourse evolve. Day three and four focus on substance use disorders and exploration of information in the Seeking Safety manual. In-depth discussions help clinicians understand how the Seeking Safety sessions are offered as well as the integration of traditional healing practices. The last day of training focuses on vicarious traumatization, practice sessions, planning and implementation.

The investigators will work with the Benbowopka team and their digitized data collection health record system. The enhancement of the digital health record could enable efficient data capture and evaluation for quality improvement, research, and reporting purposes. Benbowopka staff, patients, and the Mamawesen communities will benefit from this training and technology enhancement going forward. Importantly, the reciprocal training and skills developed by the community and research team will strongly position collaboration for future community-based research studies and will materially increase the capacity for high-quality Indigenous wellness research in northern Ontario.

Community-based trainees include three clinical staff, a graduate student, and a research assistant. The academic research team will benefit from enhancing its understanding of Indigenous Healing, unique community perspectives, and Indigenous ways of knowing.

### Data collection

The historical program data will be collected from Benbowopka’s records from January 2013 to March 2016 (end of the 2015 fiscal year). The data will be divided into fiscal year and intake period at the request of Benbowopka. Historical demographic data for each intake period will be found in the “Client Information Summary” folders in Benbowopka’s archive room.

We will use the Drug Use Screening Inventory (DUSI) to collect data on patients during the program. The DUSI and a revised version (DUSI-R) were developed by the Center for Addiction and Mental Health (CAMH) to identify consequences of alcohol and drug involvement [49]. The DUSI is a 149-item multidimensional instrument that quantifies not only involvement with drugs and alcohol, but also associated problems in the areas of mental health and psychosocial domains. The DUSI-R consists of 159 items. The following variables will be collected: name, health card number, date of birth, postal code, status card number, gender, date of admission to the program, date of discharge, program completion (Y/N), Indigenous (Y/N), status First Nation (Y/N), on reserve (Y/N), primary substance, and secondary substance(s). Drug classes from primary and secondary substances will be further divided into a sub-substance category. Any pertinent notes will also be included in the data.

The original data will include drug classes used by Benbowopka (i.e. alcohol, narcotics, prescription drugs, solvents/inhalants, and other). The revised data will be organized by the drug class preference of the research team (i.e. alcohol, cannabis, stimulants, opioids, depressants, hallucinogens, inhalants/solvents). Some drug names will be changed to ensure cohesion (e.g. brand to generic names, acid to LSD, etc.).

### Administrative data variables

The administrative data will be collected by submitting a formal requisition to ICES. All diagnostic information from physician visits will be determined using billing data from OHIP. Emergency department visits will be identified using the National Ambulatory Care Reporting System (NACRS). Hospital admissions will be identified using the Discharge Abstract Database (DAD). We will obtain patients’ location of residence and demographic information, including all-cause mortality from the Ontario Registered Persons Database (RPDB), which contains unique data for each resident who has ever received insured health.

## Choice of outcome tools: quantitative and qualitative

### Data analysis

We will evaluate the results of the IHSS intervention against three distinct primary outcomes. The lens will be applied to these outcomes considered:*The patient perspective* we will use Client Quality Assurance Survey tool to assess the **appropriateness** and **satisfaction** of the intervention*The program perspective* we will use program completion as a primary outcome to assess the **effectiveness** of the IHSS intervention*The community perspective* we will use the impact of substance use related health system usage in the year following treatment completion as an indication of the **impact** of the intervention on health system outcomes.

Specific variables to address patient wellbeing will be captured in the patient satisfaction survey and during patient aftercare follow up. Anonymized linked data outcomes from ICES will include primary care visits, mental health visits, initiation of opioid agonist therapy, emergency department visits, hospitalizations, and all-cause mortality.

A qualitative thematic analysis will be performed using the text of each pre-group individual interview, the Sharing Circles, and the facilitator interviews. Thematic analysis is a search for themes that emerge as important to the description of the phenomenon [50]. A thematic analysis will allow for a broad exploration and analysis of the impact of the Seeking Safety Sharing Circles and traditional healing methods. The process will be extensive and will include an interpretative analysis of the underlying meanings. This will be further analyzed by means of the iterative process of understanding [50–52].

Interpretation of the text will be a dialectic undertaking, shifting from understanding to explanation, and from explanation to comprehension. The process will involve the identification of themes through “careful reading and re-reading of the data” [53]. There will be a form of pattern recognition within the data, where emerging themes could become the categories for analysis. A coding process will be employed to categorize the transcribed data to reveal common themes. The interpretation process will begin with reading the text several times to gain an understanding of the entire questionnaire responses.

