This study will aim to evaluate the effectiveness of the validated treatment model (IHSS) for the treatment of Indigenous patients with a history of IGT and SUD in a four-week residential treatment centre. Study findings will be used to inform trauma and SUD residential treatment programming and implementation for Indigenous communities across Canada. Hopefully this work will contribute to the field of community-based trauma and addiction programming by addressing objectives that consider:*The patient perspective* does patient satisfaction improve when IHSS methodology for treatment of trauma and SUD replaces an abstinence-focused approach?*The program perspective* do program completion rates improve following the implementation of IHSS intervention?*The community perspective* does the revised program serve a broader range of community members requiring treatment for SUD and IGT? Does the impact of residential addiction treatment on reducing broader health care utilization (through reduced substance use related emergency room presentations and hospital admissions in the year following treatment completion) increase following IHSS implementation?

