## Methods

### Aim

The aim of this study will be to determine whether patients who are treated with the IHSS model will have improved treatment satisfaction (increase of 10% over pre-intervention rates), improved treatment completion (increase of 10% over pre-intervention rates), and a greater reduction in health system usage (substance use related presentations to emergency room and hospital admissions) at one-year follow-up compared to those treated within the abstinence-based model (decrease of 10% over pre-intervention rate).

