### Setting of the study

Benbowopka treats approximately 90 patients per year in a residential addiction treatment program in Blind River Northern Ontario. The study periods will include pre-intervention (April 1, 2013–March 31, 2016) and the post-IHSS intervention study window spanning the 27 months post-IHSS implementation (January 1, 2018–March 31, 2021; *n* > 300). Time periods will be chosen to allow analysis by both calendar year and fiscal year. On every 28-day treatment cycle, participants will be recruited and informed by the staff at Benbowopka about the study and, if interested, a consent will be obtained. The data collection will include data from patients initiating treatment at Benbowopka during the study window. Patient follow-up will occur in the year following treatment completion and/or discontinuation. Anonymized patient records will be linked via Ontario Health Insurance Plan (OHIP) number to the administrative health data at the ICES. ICES, formally known as the Institute for Clinical Evaluative Sciences, is an independent research institute that collects and analyzes data on publicly funded health services for research. The data will be queried in the one year following completion or discontinuation of IHSS at Benbowopka to ascertain the impact of substance use on health outcomes including hospitalization, emergency department visits and opioid-related overdose. For patients with multiple admissions, the date of first admission will serve as the index date for health outcomes evaluation.

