### Study population

We will only include data from first-time patients initiating treatment at Benbowopka, meaning that there will be no previous history of treatment at this center. It is common for patients to cycle between treatment and relapse. Studies have shown that multiple treatment attempts are associated with a higher likelihood of positive outcome [32]. Therefore, we will only include first-time patients to eliminate bias associated with cases involving multiple treatment attempts.

Benbowopka’s residential treatment program collects individual-level data based on standardized assessment screening tools routinely used by the Drug and Alcohol Treatment Information System and the National Native Alcohol and Drug Abuse Program. The cohort for this study will be created by using anonymized patient records from the Ontario Health Insurance Plan (OHIP) number. We will link the OHIP number to the administrative health data at ICES in order to be able to evaluate broad health outcomes for patients after they completed the treatment program. ICES routinely links partner data to its core health systems data holdings. We will then query data in the one year following completion or discontinuation of IHSS at Benbowopka to ascertain *Impact of Substance Use on Hospital Costs* as defined by the Canadian Center on Substance Abuse [42]. ICES linkage will enable virtual follow-up of Benbowopka patients for health systems usage. A detailed timeline can be found in the appendix.

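### The health-system primary outcome is tied to treatment completion in some sections and to completion or discontinuation in others; one population and window should be stated

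*Protocol article*

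**What the plan says.** The protocol article describes the one-year health-system outcome in five sections, in three ways.

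*Completion only.* The Data analysis section, where the three primary outcomes are named, says "we will use the impact of substance use related health system usage in the year following treatment completion as an indication". The community objective at the end of the Background refers to "hospital admissions in the year following treatment completion". Study population gives the purpose of the ICES linkage as being to "evaluate broad health outcomes for patients after they completed the treatment program". None of these mentions patients who leave early.

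*Completion or discontinuation.* Setting of the study says "Patient follow-up will occur in the year following treatment completion and/or discontinuation", and then "The data will be queried in the one year following completion or discontinuation of IHSS at Benbowopka". Study population repeats the same query rule directly after its completion-only sentence.

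*No start stated.* The Aim says only "at one-year follow-up compared to those treated within the abstinence-based model".

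Setting of the study also has a sentence on index dates: "the date of first admission will serve as the index date for health outcomes evaluation". That sentence opens by limiting itself to patients with multiple admissions.

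Program completion is a primary outcome in its own right (Data analysis), and the Aim expects IHSS to raise it by 10% over the pre-intervention rate.

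**The concern.** Two analysts could follow this article faithfully and analyse different patients. One, working from the outcome definition, would keep only those who completed. The other, working from the data query, would keep everyone who started.

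The choice matters because completion happens after treatment begins and is something the intervention is meant to change. If IHSS retains patients who would have left under the abstinence-based model, completers in the two periods are different mixtures of people, even when their baseline covariates balance. The propensity match on sex/gender, age and substance type (Abstract) acts on characteristics at entry and cannot correct a selection made later. A difference in emergency visits or admissions among completers could then reflect who was retained and not what the treatment did.

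This is not detail that an article can leave to a fuller plan. The article states the rule, and states it both ways.

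**Working it through.** **1. The sections side by side**

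| Section | Year starts after | Early leavers covered by the wording? |
|---|---|---|
| Background, community objective | completion | no |
| Aim | not stated | not stated |
| Setting, follow-up sentence | completion and/or discontinuation | yes |
| Setting, query sentence | completion or discontinuation | yes |
| Study population, linkage purpose | completion | no |
| Study population, query sentence | completion or discontinuation | yes |
| Data analysis, primary outcome | completion | no |

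Three statements name completion only and three include discontinuation. The Propensity score matching section compares the pre and post groups and does not mention completion status. The query sentences also describe the window as following IHSS, which does not literally define it for the pre-intervention cohort.

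**2. What a literal completers-only comparison could do**

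The plan gives no figure on this point to reproduce: neither completion rates nor event rates appear. The following is therefore an illustration on assumed inputs.

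- p0, completion before IHSS: 50% to 80% (assumed).
- p1, completion after: p0 + 0.10 or 1.10 × p0. The Aim's 10% can be read either way.
- a, one-year event risk in patients who would complete under either model: 0.20 or 0.30 (assumed).
- h, risk in the extra completers: 0.40 (assumed).
- IHSS has no effect on events, and nobody who would have completed before leaves early under IHSS (assumed).

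Risk among completers is a before IHSS and [p0 × a + (p1 − p0) × h] / p1 after. Hence

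RR = 1 + [(p1 − p0) / p1] × (h/a − 1).

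- Largest value: p0 = 0.50, p1 = 0.60, a = 0.20. After: (0.50 × 0.20 + 0.10 × 0.40)/0.60 = 0.14/0.60 = 0.233, against 0.200 before. RR = 1.17.
- Smallest value: a relative 10% rise gives (p1 − p0)/p1 = 0.10/1.10 = 0.0909 for any p0. With a = 0.30, RR = 1 + 0.0909 × (0.40/0.30 − 1) = 1.03.
- Equal risk, h = a: RR = 1.00.
- Extra completers at lower risk, for example p0 = 0.60, p1 = 0.70, a = 0.30, h = 0.20: (0.18 + 0.02)/0.70 = 0.286 against 0.300. RR = 0.95.

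**3. The same null case with everyone counted**

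Take p0 = 0.60, p1 = 0.70, a = 0.20, h = 0.40, and 0.40 for those who complete under neither model. Overall risk is 0.60 × 0.20 + 0.10 × 0.40 + 0.30 × 0.40 = 0.28 in both periods. RR = 1.00. Moving patients from non-completion to completion leaves the comparison unchanged when all of them are counted.

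**The case against.** The strongest reply is that the completion-only phrases are shorthand. They name a time window, not a population. The sections that do define the population take patients who start treatment at the centre for the first time, the follow-up and query sentences cover discontinuation three times, and nothing in the article excludes non-completers. This stands. A reader might infer that the plan commits to a completers-only analysis; the documents do not support that. What remains is that the section fixing the primary outcome omits discontinuation, and nothing says that the query wording overrides it.

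A reader might also infer a third, conflicting clock that starts at admission. The sentence behind that inference applies only to patients with multiple admissions, and most naturally says which episode counts. It deserves a clarifying word but is not an established contradiction. Nor do the documents show that the year should run from admission. The stated interest is use after treatment, and an admission clock would bring up to about 28 days of residence (28/365 = 7.7% of the year) into the window. A discharge clock does start sooner for early leavers than for completers, but that is not shown to be an error.

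Finally, the size of the bias is assumed, and it may be small beside sampling error. Suppose 300 patients per period, completion of 60% and 70% (180 and 210 completers), and risks of 30% and 45% in the two kinds of completer. The completers-only rates are then 30.0% and (0.60 × 0.30 + 0.10 × 0.45)/0.70 = 32.1%. The 2.1-point shift is about 0.46 of its unmatched standard error, √(0.300 × 0.700/180 + 0.321 × 0.679/210) = 4.7 points. That is fair, and it argues against any claim of a large known distortion. It does not argue for leaving the population open, because a selection bias does not shrink as patients accrue.

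**Conclusion.** The inconsistency is real, lies in the current text and concerns a primary outcome. Read literally, the outcome definition conditions on completion, which is another primary outcome and one that IHSS is expected to raise. That could bias the comparison in either direction, by an amount the documents do not allow to be computed.

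Under the assumed rates and no true effect, the completers-only RR runs from about 1.03 to 1.17 if the extra completers are at higher risk, is 1.00 if their risk is equal, and falls below 1 if it is lower. The upper part of that range is comparable in size with the 10% decrease sought in the Aim. It would be tempting to say that completers-only analysis makes IHSS look worse because it retained harder cases. That direction follows from the risks one assumes, not from anything in the plan.

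Since the operational sections already cover everyone who starts treatment, this is a definition to be made consistent before the linked data are analysed. It is not evidence that the wrong analysis is planned.

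**What to change.** In the Background objective, Study population and Data analysis, state one rule: the health-system outcome is analysed in all patients starting treatment at the centre for the first time, whether or not they complete, over the one year following completion or discontinuation, counted from the discharge date. Say that the rule applies identically to the pre- and post-IHSS cohorts, and reword the query sentences so that they no longer refer to IHSS alone. Any completers-only analysis should be labelled a sensitivity analysis.

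In Setting of the study, clarify that the first-admission sentence selects which episode counts for a patient admitted more than once.

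The cost is a wording amendment. Admission date, discharge date and completion status are already collected (Data collection), and patients who discontinue are already in the planned query. A window starting at admission may be added as a sensitivity analysis but is not required. It would need a wider request to ICES, because events between admission and discharge fall outside the query as now described.

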### Propensity score matching

Logistic regression will be used to define propensity scores for treatment groups (pre and post intervention). The treatment group will be matched 1:1 to control using a caliper width of 0.20 greedy matching [54]. Standardized differences (d) will be calculated for each covariate before and after matching. Standardized difference (d) less than 0.10 will indicate balanced covariates [55]. Propensity score matched data will be analyzed to calculate the effect of receiving treatment post-intervention on each helth system usage outcome using McNemar’s test [56]. Proportions will be used to calculate clinical descriptors including relative risk (RR) and number needed to treat or number needed to harm (NNT/NNH), along with 95% confidence intervals (CI) for each descriptor calculated. All statistical analysis will be conducted on the remote server using SAS Version 9.4 [57]. Data will be reviewed by ICES to insure privacy standards are met.

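### The community primary outcome is described in several different ways with no rule for combining its parts, and each usage outcome is then tested separately

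*Protocol article*

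**What the plan says.** Data analysis declares "three distinct primary outcomes", one each for the patient, programme and community perspectives. The community outcome appears in these forms:

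- **Background (closing objectives):** one question is "does the revised program serve a broader range of community members requiring treatment for SUD and IGT". A second concerns "reduced substance use related emergency room presentations and hospital admissions in the year following treatment completion".
- **Aim:** "substance use related presentations to emergency room and hospital admissions", with a 10% decrease as the target.
- **Setting of the study:** the linked data will be queried for "health outcomes including hospitalization, emergency department visits and opioid-related overdose".
- **Study population:** the same one-year query is meant to ascertain "Impact of Substance Use on Hospital Costs", using an external body's definition.
- **Data analysis, primary outcome statement:** substance-related health system usage in the year after completion, with no components named.
- **Data analysis, next paragraph:** the linked outcomes will include "primary care visits, mental health visits, initiation of opioid agonist therapy, emergency department visits, hospitalizations, and all-cause mortality". These are not labelled primary or secondary.

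Propensity score matching then says the matched data will be used to estimate "the effect of receiving treatment post-intervention on each helth system usage outcome" by McNemar's test. No section names a composite, a lead component, an order of testing or a division of alpha for this outcome.

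**The concern.** An article may leave code lists and similar detail to a fuller document. Here, though, the article itself gives different answers to what one of its three primary outcomes is. The Aim joins two events without saying whether they form one endpoint or two, and the analysis section then tests usage outcomes one at a time. An analyst who followed the text could report the community objective as met if either component were significant. Under the Setting wording, overdose would offer a further chance.

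Some versions also do not fit the planned test. McNemar's test needs a paired yes/no outcome. A cost, or a count of visits, cannot be tested that way unless it is first dichotomised, and the article does not say how that would be done.

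The start of the follow-up year differs as well. The Background objectives and the primary outcome statement count from completion. Setting of the study and Study population count from completion or discontinuation. Completion is itself a primary outcome that the intervention is meant to change, so the two versions define different analysis populations.

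**Working it through.** **1. The plan's own figure.** Design gives an effect size of 0.5, a probability level of 0.05, power above 80% and 65 patients per group. For two means, two-sided, under the normal approximation:

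n = 2 × [(1.960 + 0.842) / 0.5]² = 62.8, so 63 per group.

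The t-test version gives 64. At 65 per group, power is 0.81 by either method. The stated figure reproduces, so the point does not rest on an arithmetic error. It is, however, a calculation for one continuous comparison at an undivided 0.05. It does not address several paired binary tests.

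**2. Counting the tests.** The Aim names two components, emergency visits and admissions. With no combining rule, and a test for *each* usage outcome, the minimum is two community tests. Satisfaction and completion, at one test each, make four.

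**3. Chance of at least one false positive.** For k independent tests at 0.05 this is 1 − 0.95^k.

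| Reading | k | Result |
|---|---|---|
| One fixed community endpoint | 1 | 5.0% |
| Community: emergency visits and admissions | 2 | 9.8% |
| Community: the three items in Setting of the study | 3 | 14.3% |
| Three primaries, community fixed as one endpoint | 3 | 14.3% |
| Three primaries, community as two tests | 4 | 18.5% |

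Independence is an assumption. Emergency visits, admissions and overdoses are likely to overlap in the same patients, and positive correlation lowers these figures.

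**4. Power cost of a joint rule.** The article gives no baseline event rates, so I assume 20% and 50%. I read the 10% target as percentage points (the Aim does not say which), take 300 per group from Design, and use an unpaired approximation:

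power = Φ[(d − z × se0) / se1], where se0 is the pooled and se1 the unpooled standard error.

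- *20% to 10%:* se0 = √(0.15 × 0.85 × 2/300) = 0.02915 and se1 = √((0.16 + 0.09)/300) = 0.02887. At 0.05 (z = 1.960) power is 0.93. At Holm's first step, 0.05/3 = 0.0167 (z = 2.394), it is 0.85.
- *50% to 40%:* se0 = √(0.45 × 0.55 × 2/300) = 0.04062 and se1 = √((0.25 + 0.24)/300) = 0.04041. Power is 0.69 at 0.05 and 0.53 at 0.0167.

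Adjusting across all three primaries is therefore not free.

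**The case against.** The best reply is that the article is more consistent than a list of its wordings suggests. The Background objectives and the Aim name the same two substance-related components, and the primary outcome statement keeps the substance-related limit. The hospital-costs phrase is italicised and tied to an external definition that is not available here, so it may label a definition of substance-attributable hospital use and not a cost endpoint. Code lists, alpha allocation and the ranking of secondary variables commonly sit in an analysis plan. The three primaries answer separate questions, so adjustment across them is open to debate.

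Most of this stands, and it limits the point. A reader might go further and infer three things that the documents do not support:

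- **Six linked outcomes as primaries, giving eight tests and 33.7%.** The list is a separate paragraph and is never called primary. All-cause mortality in it is not a usage outcome either.
- **Outcomes pulling in opposite directions under one target.** The 10% decrease attaches only to substance-related emergency visits and admissions. No decrease is set for primary care visits, mental health visits or opioid agonist initiation.
- **Dilution by all-cause visits.** The primary outcome statement is limited to substance-related usage, so the missing qualifier in the later list does not make the primary all-cause.

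The reply does not supply a combining rule for the Aim's two components. It does not explain the different content in Setting of the study, or settle which outcomes the word *each* covers.

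**Conclusion.** The point holds as an inconsistency in the article's own text. The community primary outcome has no single definition, and the stated analysis allows more than one test of it. The firm count is two community tests and four across the primaries, giving 9.8% and 18.5% at 0.05. Both figures assume independent tests and that *each* covers emergency visits and admissions separately. They would be lower with positive correlation. Of the 18.5%, 14.3% would arise from three primaries at 0.05 each even with the community endpoint fixed. Whether that part needs control depends on whether the three are read as separate questions, which the article should state. The conflict over the start of follow-up is a further contradiction to resolve.

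**What to change.** 1. Define one binary community primary that suits McNemar's test. An example is any substance-related emergency visit or hospital admission within 365 days, with the same definition in both eras. A sum of visits and admissions would be a count and would not fit the planned test.
2. Use that definition in the Background objectives, Aim, Setting of the study, Study population, Data analysis and Propensity score matching.
3. Choose one start for the follow-up year, completion or completion/discontinuation, and apply it in the same sections.
4. Label overdose, cost, the separate components and the other linked outcomes as secondary.
5. State whether the three primaries are separate questions at 0.05 each or are governed by a joint rule. Holm and a requirement that all three succeed are very different rules and should not be treated as interchangeable. If Holm is chosen, state its power cost.

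Steps 1 to 4 change wording only. Emergency visits and admissions already come from the linked sources named under Administrative data variables, so no new data are needed. Step 5 costs nothing if the primaries stay separate. Under the assumptions in the working, Holm's first step would lower power from 0.93 to 0.85 at a 20% baseline, or from 0.69 to 0.53 at 50%.
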